# A phase II study in advanced cancer patients to evaluate the early transition to palliative care (the PREPArE trial): protocol study for a randomized controlled trial

**DOI:** 10.1186/s13063-015-0655-8

**Published:** 2015-04-12

**Keywords:** depression, neoplasms, palliative care, cognitive behavioral therapy

## Abstract

**Background:**

Previous studies have demonstrated the benefit of early integration of palliative care (PC) in oncology. However, patients continue to receive late referrals to PC even in comprehensive cancer centers. Patients and health professionals may perceive PC as ‘a place to die,’ and this stigma is a barrier to timely referrals and to patient acceptance of treatment.

**Methods/design:**

The primary objective is to evaluate the feasibility of psychosocial intervention and PC in patients with advanced cancer. The patients will be submitted to a series of brief psychosocial interventions that are based on cognitive behavioral therapy, and patient acceptance and satisfaction will be assessed. In addition, the impact of these interventions on depressive symptoms will be evaluated. A randomized, open-label, phase II trial with two intervention arms and a control group will be conducted. Patients who are started on palliative chemotherapy and who meet the inclusion criteria will be enrolled. The study participants will be recruited from the outpatient oncology clinics at Barretos Cancer Hospital and will be randomized into one of the following three treatment arms: Arm A, which will include five weekly psychosocial interventions based on CBT in combination with early PC; Arm B, which will include early PC only; and Arm C, which will include standard oncologic care. The Hospital Anxiety and Depression Scale (HADS), the Patient Health Questionnaire (PHQ-9), the Edmonton Symptom Assessment System (ESAS-br), the Family Satisfaction with End-of-Life Care (FAMCARE)-Patient scale, and the Disease Understanding Protocol will be used for data collection. The patients will answer these questionnaires at baseline and 45, 90, 120 and 180 days after randomization.

**Discussion:**

Despite evidence of the positive impact of early PC, it is often provided to patients only at later stages. The inadequate awareness and stigmatization of PC as a place to die are barriers that complicate the early referral. Patients with advanced cancer may benefit from a psychosocial and educational strategy that adequately prepares them for initial PC appointments after an early referral to PC. We anticipate that benefits of psychological intervention shall be synergistic to secondary emotional benefits from the early integration of PC.

**Trial registration:**

This trial was registered on 6 May 2014 with ClinicalTrials.gov (identifier: NCT02133274).

**Electronic supplementary material:**

The online version of this article (doi:10.1186/s13063-015-0655-8) contains supplementary material, which is available to authorized users.

## Background

Approximately 32.6 million people worldwide are living with cancer that has been diagnosed within the last five years [1]. Many cancer cases are diagnosed as metastatic disease despite advances in cancer prevention strategies. Furthermore, a significant portion of these cases are associated with disease recurrence during the monitoring period. These advanced disease cases are eligible for concurrent or exclusive monitoring by specialized palliative care (PC) teams. Approximately 6.5 million cancer patients are in PC worldwide [2].

The World Health Organization has defined PC as ‘an approach that improves the quality of life (QL) of patients and families who face a life-threatening illness through the prevention and relief of suffering. This approach is based on the early identification, assessment, and treatment of pain and other physical, psychosocial, and spiritual problems’ [3]. Therefore, PC should be provided by a multidisciplinary team that acts integrally in outpatient, hospital, and/or home environments [4,5].

Temel *et al*. [6] evaluated the early integration of PC in non-small cell lung cancer patients who were starting first-line palliative chemotherapy. An improvement in the QL scores and a decrease in the symptoms of depression were evident 12 weeks after randomization. Furthermore, they found that the patients who received early PC were submitted to fewer aggressive treatments in the final stages of life. A post-hoc analysis inclusively demonstrated a 2.7-month increase in the overall survival rate of patients who received PC. A study by Bakitas *et al*. [7] evaluated the early introduction of a psychoeducational program in the treatment of cancer patients from rural areas in the United States. The authors observed improved QL scores and reduced symptoms of depression over time. More recently, a cluster randomized clinical trial [8] evaluated the early introduction of PC in a general oncology population in Canada. The main objective of this study was to improve the spiritual QL of patients 3 months after randomization. Improvements in the overall QL at 3 and 4 months after randomization, the spiritual QL after 4 months and patient satisfaction were observed in the patients who received early PC.

Despite evidence of the positive impact of early PC on the progress of cancer patients, PC is often provided to patients at later stages even at oncology and PC reference centers [9]. In Brazil, reliable information on how and when cancer patients are referred to PC is lacking; however, we believe that patients are referred late to PC. The inadequate awareness and stigmatization of PC, which is perceived as a place to die, are barriers that complicate the early referral of patients to PC [10,11]. The title ‘Palliative Care’, which implies improvisation or something provisional, has complicated patient acceptance of PC within the context of early cancer support during chemotherapy. Patients who are referred to PC are often anxious at the first appointment [12], which leads to a high absenteeism rate.

Therefore, the main hypothesis of the present study is that patients with advanced cancer may benefit from a psychosocial and educational strategy that adequately prepares them for initial PC appointments after an early referral to PC.

## Methods/design

### Main objectives

The main objectives of this study are as follows:To assess the feasibility of a brief psychosocial intervention based on cognitive behavioral therapy (CBT) and early PC in advanced cancer patients, including patient acceptance and satisfaction.To assess the impact of the intervention on symptoms of depression at 90 days after randomization and to compare the differences between the intervention groups and the control group and between the intervention groups.

### Secondary objectives

The secondary objectives of the study are as follows:To assess the impact of the interventions on symptoms of depression at 45, 120 and 180 days after randomization and to compare the differences between the intervention groups and the control group and between the intervention groups.To assess the impact of the interventions on anxiety symptoms at 45, 90, 120 and 180 days after randomization and to compare the differences between the intervention groups and the control group and between the intervention groups.To assess the impact of the interventions on the QL scores at 45, 90, 120 and 180 days after randomization and to compare the differences between the intervention groups and the control group and between the intervention groups;To assess the impact of the interventions on symptom scores (pain, fatigue, nausea, drowsiness, anorexia, dyspnea, and insomnia) at 45, 90, 120 and 180 days after randomization and to compare the differences between the intervention groups and the control group and between the intervention groups.To assess the differences in disease awareness at 45, 90, 120 and 180 days after randomization in the three arms of the trial.To assess the differences in the number of invasive procedures at the end of life, such as intensive care unit admissions and chemotherapy during the last 14 to 28 days of life, between the treatment arms.

### Study design

This study will be a randomized open-label, phase II clinical trial with two intervention arms and a control group. Figure 1 summarizes the study design.

**Figure 1 Fig1:**
[figure not shown]
Study flowchart.

### Eligibility criteria

#### Inclusion criteria

Age ≥18 years and <75 years.Adequate knowledge about the cancer diagnosis.First-line palliative chemotherapy.Eastern Cooperative Oncology Group Performance Status (ECOG-PS) ≤2.Life expectancy >6 months and <24 months (according to the medical oncologist).One of the following diagnoses: metastatic or unresectable recurrent breast cancer, stage IIIC or IV recurrent platinum-resistant ovarian cancer, metastatic or unresectable recurrent cervix cancer, metastatic or unresectable recurrent endometrial cancer, metastatic or unresectable recurrent head and neck cancer (after previous radiotherapy), hormone-refractory metastatic or unresectable recurrent prostate cancer, metastatic or unresectable recurrent genitourinary cancer, metastatic or unresectable recurrent non-small cell lung cancer, extensive-stage or recurrent small cell lung cancer, or metastatic or unresectable recurrent gastrointestinal cancer.

#### Exclusion criteria

Patients can be excluded from the study for any of the following:Any current psychological treatment due to a psychological disorder.Current antidepressant use to treat depressive disorders and/or anxiety.Regular follow-up in the PC department due to advanced cancer or an immediate referral to PC by the assistant physician.Any cognitive deficit or attention problem that could interfere with the ability of patients to answer questionnaires or understand the study aims (according to the investigator).A current or previously established diagnosis of any of the following psychological conditions: substance-related disorders, schizophrenia and other psychotic disorders, mood disorders (depressive disorders, bipolar disorders), anxiety disorders, dissociative disorders, personality disorders, and/or a history of a suicide attempt.Single resected metastasis.Any comorbid condition that would interfere with patient safety, compliance with the study, or the interpretation of the results according to the investigator.

### Data collection and randomization

The psychological intervention will be conducted by psychologists trained for the study. Data collection will be conducted by a team of research coordinators from the Center for Research Support at Barretos Cancer Hospital (BCH; Barretos, SP, Brazil).

A trained member of the Center for Research Support, not involved in data collection or statistical analysis, was assigned to handle the randomization process, using tables of random numbers. The study participants will be randomized (1:1:1) into arms A, B or C. Randomization will be based on blocks of six patients and will be stratified as follows: breast, gynecological, gastrointestinal, urological, head and neck, and thoracic. The study arms will be as follows:Arm A (experimental): psychosocial plus early PC, including five weekly psychosocial interventions based on CBT plus early PC (a first medical consult at the Palliative Care Service will be scheduled for 2 to 3 weeks from the study inclusion date and every 3 to 4 weeks thereafter).Arm B (experimental): early PC (a first medical consult at the Palliative Care Service will be scheduled for 2 to 3 weeks from the study inclusion date and every 3 to 4 weeks thereafter).Arm C (no intervention): standard oncologic care.

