The attribution of meaning is important for detecting maladaptive behaviors, which are modifiable through interventions according to CBT [30]. CBT is based on the premise that cognition affects behavior; however, cognition may be monitored and changed and the desired behavioral change may be achieved through cognitive change [31]. CBT aims to enable individuals to identify and modify their distorted or dysfunctional automatic thoughts [32]. Evidence suggests that CBT may benefit advanced-stage cancer patients by reducing anxiety symptoms, improving QL [33], and decreasing psychiatric disorders, which have been observed in cancer patients who were classified as high-risk for the development of such disorders [25]. Therefore, the study population in the present study (advanced-stage cancer patients who start palliative chemotherapy) may be considered at a high risk for developing depression. Psychoeducation is another key tool used in CBT. In a previous clinical trial, cancer patients were submitted to a psychoeducational intervention. This strategy was effective in improving disease awareness rates, and the patients were better equipped to deal with problems, had lower levels of isolation and guilt, and felt a sense of belonging to the group. A broad sharing of experiences and lessons by other patients with advanced cancer was observed [34].

The strategy that has been proposed in this study is novel and has not yet been assessed in this context. BCH receives patients from all of the states in Brazil, particularly patients from the Southeast, Midwest and North regions because this hospital is recognized as a reference institution in the Brazilian public health system. Despite being monocentric, this study will assess the impact of the intervention in a culturally heterogeneous population with different needs, and the results of this study may be generalized to the entire Brazilian population.

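### A single published block length of six, within tumour-site strata of an open-label single-centre trial, makes up to 28.9% of allocations predictable as early palliative care (PC) or none to anyone tracking a stratum

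*Protocol article*

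**What the plan says.** All of the following is in the protocol article.

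- **Data collection and randomization:** "The study participants will be randomized (1:1:1) into arms A, B or C", and "Randomization will be based on blocks of six patients and will be stratified as follows", the strata being "breast, gynecological, gastrointestinal, urological, head and neck, and thoracic". The staff member responsible was "not involved in data collection or statistical analysis, was assigned to handle the randomization process, using tables of random numbers".
- **Study design:** "This study will be a randomized open-label, phase II clinical trial with two intervention arms and a control group". Earlier allocations can therefore be seen.
- **Discussion:** one centre ("Despite being monocentric, this study will assess the impact of the intervention in a culturally heterogeneous population").
- **Inclusion and exclusion criteria:** two entry conditions rest on a physician's judgement, namely "Life expectancy >6 months and <24 months (according to the medical oncologist") and, as a reason for exclusion, "an immediate referral to PC by the assistant physician".
- **Timing:** the article is dated 12 April 2015. Trial status gives August 2014 as the start of enrolment and January 2017 as the expected last inclusion.
- **Sample size calculation:** 50 patients per arm, so 150 in all.
- **Early palliative care:** Arm C patients may have a routine PC evaluation if the oncologist indicates it.

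**The concern.** With two places per arm in every block of six, the last places in a block follow from the earlier ones. Someone who knows the length and has seen the earlier allocations in a stratum can sometimes work out the next one before deciding whether to enrol a patient. The usual barriers are weak here: arms are visible, there is one centre, and the length was printed during accrual.

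The entry criteria leave room to act on such knowledge. A physician who foresees Arm C could refer the patient to PC at once, which makes the patient ineligible, or could judge life expectancy to lie outside the range. Patients entering Arm C could then differ from those entering Arms A and B.

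Two of the primary outcomes, depressive symptoms and satisfaction with care, are self-reported. The effect size is also meant to inform a phase III trial, so a bias at entry would carry forward.

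**Working it through.** **Inputs.** Block length 6, ratio 1:1:1, six strata (Data collection and randomization); 150 patients = 3 × 50 (Sample size calculation). The article gives no predictability figure to reproduce. The 90 orderings of AABBCC are equally likely.

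**1. Certainty about early PC versus none.** An allocation is certain when the places left in the block contain no C, or only C. The two Cs can occupy any of 15 pairs of positions, so by position:

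| Position | No C left | Only C left | Certain |
|---|---|---|---|
| 1 | 0 | 0 | 0 |
| 2 | 0 | 0 | 0 |
| 3 | 1/15 | 0 | 1/15 |
| 4 | 3/15 | 0 | 3/15 |
| 5 | 6/15 | 1/15 | 7/15 |
| 6 | 10/15 | 5/15 | 15/15 |
| Sum | 20/15 | 6/15 | 26/15 |

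Dividing by 6 gives 28.9% certain in total: 22.2% certain early PC and 6.7% certain Arm C. In patients, 0.289 × 150 = 43 and 0.067 × 150 = 10.

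**2. Unfinished last blocks.** With 25 patients in each stratum (150/6, assuming equal strata) there are four full blocks and one extra patient: 4 × 26/15 = 6.93, and 6.93/25 = 27.7%. Letting stratum sizes vary at random around equal or unequal shares gives 26.7% on average (range 25.3% to 28.9%), about 40 of 150.

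**3. Timing.** About 8 of the 29 accrual months precede publication and about 21 follow it. If accrual is even and the length became known only through the article, 150 × 21/29 ≈ 109 patients are exposed. That gives 0.267 × 109 ≈ 29 certain allocations, of which 0.067 × 109 ≈ 7 are certain Arm C.

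**4. Other measures, complete blocks.** The exact arm is certain at position 5 with probability 1/5 and always at position 6: (1/5 + 1)/6 = 20.0%. The best guess among three arms is right with probability 1/3, 2/5, 1/2, 8/15, 3/5 and 1 at positions 1 to 6, a mean of 56.1% against 33.3% by chance. The best guess of early PC versus none is right in 74.4%, against 66.7% (4/6) for always guessing early PC, a gain of about 8 points.

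**5. Effect of varying lengths.** This was simulated with 25 patients per stratum and lengths equally likely. The tracker is assumed to know the set of lengths, to have seen every allocation and to weigh all block boundaries that fit.

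| Lengths | Certain early PC vs none | Best guess of arm correct |
|---|---|---|
| 6 only | about 28% | 55% |
| 3, 6, 9 | about 5% | 54% |
| 6, 9, 12 | 3.5% | 51% |

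Including blocks of 3 helps less because they are predictable themselves. For a single known length of 3k, the certain share is [2k/(k+1) + k/(2k+1)]/(3k). This is 44.4% for 3, 28.9% for 6, 21.4% for 9 and 17.0% for 12.

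**The case against.** - **The list is held independently.** This protects the list itself, but it does not stop inference from allocations already seen. The objection fails on this point.
- **Concealment detail belongs in the full protocol.** That is so, and its absence from the article is not held against the plan. The point concerns what the article does fix: one block length, published during accrual.
- **The 28.9% does not match the mechanism.** A reader might infer that about 43 patients are open to manipulation. The documents do not support that. The diversion route applies when Arm C is foreseen, which is 6.7 points or about 10 patients. Nothing in the article suggests why certainty of early PC would distort entry. This objection stands.
- **56% against 33% looks dramatic.** Those figures concern guessing among three arms. For early PC versus none the gain is about 8 points. This also stands.
- **Motive and opportunity are not shown.** Arm C patients can be evaluated by PC when indicated, so a physician need not keep a patient out of the trial to obtain PC. That evaluation is not the scheduled early PC of Arms A and B, so the incentive is weakened rather than removed. The article describes late referral and stigma, not eagerness for PC. It does not say who enrols, who sees earlier allocations, or whether anyone knew the block length before publication. All this limits the claim to a possibility.
- **Baseline data help.** The depression and satisfaction outcomes are changes from baseline, and arms are compared at baseline. It would be too strong to say that no analysis could help: adjustment can deal with selection on what was measured, but not on unmeasured prognosis or distress.
- **The study is preliminary.** True, and this keeps the point minor.

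**Conclusion.** The point holds as a minor, avoidable design weakness. The share of allocations certain as early PC or none is at most 28.9%, and about 27–28% (roughly 40 of 150) once unfinished last blocks are counted. About 10 of 150 are certain Arm C, the group for which the diversion route is plausible.

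These are ceilings. They assume that the length is always six, which is the plain reading of the article, that the recruiter knows it throughout, and that every allocation in the stratum is tracked. If the length was learned only from publication, the counts are nearer 29 and 7.

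A reader might conclude that recruiters did know these allocations, or that the comparison is biased. The documents support neither; they show only that the design permits it.

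**What to change.** For all blocks not yet opened, the same randomisation handler should generate new lists within each stratum, with block lengths drawn at random from multiples of three, for example 6, 9 and 12. The lengths should be kept out of any document that recruiters see. Allocations already made stay as they are, and the ratio and the strata do not change.

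The gain is mainly in certainty, which falls from about 28% to about 4% even if the set of lengths leaks. The best guess of the arm improves little (55% to 51%), so the change should not be presented as making allocation unpredictable. Lengths of 3, 6 and 9 would also serve, but do less on both measures (about 5% and 54%).

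The cost is one new set of lists and slightly more possible imbalance where a stratum ends mid-block. The largest possible difference between two arms from an unfinished block rises from 2 patients (6/3) to 4 (12/3), or to 3 (9/3) if 9 is the longest block.

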### Measures

The Hospital Anxiety and Depression Scale (HADS) is a widely used tool for screening cancer patients for anxiety and depression [13]. The HADS consists of 14 items that are divided into two subscales of seven items each (HADS-A and HADS-D). The score for each item ranges from 0 to 3. A score of 0 is the minimum score for each subscale, and 21 is the maximum score. The psychometric properties of HADS have previously been assessed in the Brazilian population and are considered adequate [14].

The Patient Health Questionnaire (PHQ-9) is derived from the Primary Care Evaluation of Mental Disorders (PRIME-MD) screening questionnaire for depressive symptoms, which was originally developed to screen patients for depression, anxiety, alcohol abuse, somatoform disorders, and eating disorders [15]. The PHQ-9 was validated for use in Brazil in 2013 and is considered a useful tool for screening depression symptoms [16]. The PHQ-9 consists of nine questions that examine the presence of major depressive episode symptoms (Diagnostic and Statistical Manual of Mental Disorders IV, DSM-IV) using the 4-point Likert scale (0 to 3) for a total of 27 points.

The European Organization for Research and Treatment of Cancer Quality of Life Questionnaire Core 15 Pal (EORTC QLQ-C15-Pal) consists of 15 items, and 14 of these items are answered using 4-point Likert-type scales (1 to 4). In addition, a single item assesses overall QL, which is measured using a numerical scale that ranges from 1 to 7. The QLQ-C15-Pal assesses two functional scales (physical and emotional), two symptom scales (fatigue and pain), and five single-item scales (nausea/vomiting, dyspnea, insomnia, loss of appetite, and constipation) [17]. The EORTC-QLQ-C15-Pal was validated for use in Brazil in 2013 with adequate psychometric properties [18].

The Brazilian version of the Edmonton Symptom Assessment Scale (ESAS-br) consists of a visual numeric scale with scores of 0 to 10 to assess ten symptoms, including pain, fatigue, drowsiness, nausea, depression, anxiety, loss of appetite, feeling of wellness, breathlessness, and insomnia [19]. The ESAS-br was associated with adequate psychometric properties when used in a Brazilian population ([name] *et al*., unpublished data).

The Disease Awareness Protocol is a translated version of the protocol on cancer awareness and treatment that was used by Temel *et al*. and was adapted for this study [6]. This protocol assesses patient perception regarding their chance of a cure and the objective of chemotherapy (see Additional file 1).

The Family Satisfaction with End-of-Life Care (FAMCARE)-Patient scale, originally titled FAMCARE, was developed to assess the satisfaction of family caregivers of advanced cancer patients with healthcare [20]. Subsequently, Lo *et al*. [21] modified the original items to transform this instrument into a 16-item scale for assessing the satisfaction of patients with advanced cancer who undergo outpatient treatment. The most current version of the scale includes 13 items with 5-point Likert-type scale responses that range from ‘very dissatisfied’ (a score of 1) to ‘very satisfied’ (a score of 5) [22]. One item, ‘emotional support provided by the healthcare team’, was added to this questionnaire in the present study because of the nature of the intervention under study. The Portuguese version that was used in the study underwent translation, cultural adaptation, and pre-testing according to Beaton *et al*. [23].

